### Data management and quality control

Data will be managed using Research Electronic Data Capture (REDCap), including regulatory document management, data entry and validation, source document and progress monitoring, subject tracking, and secure data transfer [71, 72]. During study initiation, weekly communication will occur with each site via video conference. During these initial meetings, REDCap data fields and entry will be reviewed in detail, tested at each site, and troubleshooting and modification will occur as needed to streamline efficient data entry. Throughout the study, data checks for valid ranges and completeness of data will occur. We will track and identify for each subject the study forms that are expected but not yet entered into REDCap. All site personnel will have ability to run reports that will provide detailed lists of expected forms and of all data queries for their site. In addition, the CCC will provide reports to site investigators, as needed, for timely submission of data forms and resolution of queries. All data will be entered into REDCap by site personnel.

Excluding questionnaires, all data will be obtained from the medical record and verified before data entry. In REDCap, validation rules will ensure acceptable ranges, and valid and accurate data, which will be monitored for errors on an ongoing basis. Any concerns or discrepancies will be resolved by study sites and the CCC; re-training will occur as needed. Routine monthly and ad hoc reports will be run as part of quality control. The reports will track patient accrual and status, data completeness, and responses to data queries.

Data entered into REDCap will be stored on Washington University servers. User privileges related to data management, beyond data entry, will be restricted. As standard operating procedure, use of REDCap to enter and store data, in a secure and password-protected manner, provides certainty that data will not be lost. After study completion, de-identified data will be exported into a statistical analysis package and analyses will proceed in a way such that patient confidentiality is maintained.

### Safety monitoring

A data and safety monitoring board (DSMB), independent of the research team and sponsor, will be used to monitor the data. The DSMB will assess safety and efficacy of trial procedures and monitor the overall conduct of the trial. The DSMB also will review adverse event data, other safety data, quality and completeness of data, protocol adherence data, and enrollment data at each meeting to ensure proper trial conduct and continued feasibility of answering the research questions. Meetings between the research team and the DSMB will occur before the study begins, after 25% of the total sample size is accrued each time, and upon trial completion.

The intervention is designed to enhance patient safety by quality improvement related to the selection of neuromuscular blockers by clinicians. Consequently, we aim to see an increase in succinylcholine use during the intervention phase of the trial, which is congruent to clinical practice for more than 40 years and consistent with recommendations for preventing awareness with paralysis. There is over a decade of research on tens of thousands of patients showing equivalent intubation success rates between succinylcholine and rocuronium. In addition, intubation success rate in the ED approaches 100% [14, 54]. We therefore, do not expect to see any difference in intubation success rate between the control and intervention phases, but will track and report this measure. Given the typically small and transient increase in serum potassium of ~ 0.5 to 1 mEq/L known to occur with succinylcholine, there is the potential for an increase in cardiac arrhythmias related to hyperkalemia to occur in the intervention phase. The overall incidence of cardiac dysrhythmia in the peri-intubation period in the ED is approximately 0.7% with no difference between succinylcholine and rocuronium. We therefore do not expect to see any difference in this adverse event between the control and intervention phases, but will track and report this measure [14]. Other very rare adverse events associated with succinylcholine include malignant hyperthermia (incidence ~ 0.009%) and allergic reaction to succinylcholine (incidence 0.01%) [73, 74]. Both of these adverse events are quite unlikely to occur, but will be tracked and reported. Unexpected events will be reported by the site principle investigators to the CCC as detected.

Adverse events and serious adverse events will be presented at each DSMB meeting. Adverse events will be classified according to severity, relatedness, and expectedness. Each site principle investigator will designate their first impression of the seriousness and relatedness of the adverse events, and this will be forwarded to a centralized independent safety monitor, who will adjudicate final relatedness, seriousness, and expectedness. As the control phase is entirely observational, this review process will pertain to sites after their transition to the intervention phase of the trial. Events will be reported in trial publications.

As the adverse events related to the choice of a particular neuromuscular blocker are so rare, and most adverse events will be related to critical illness itself, we have not established formal stopping rules. Recommendations by the DSMB will be made based on the assessment of clinical outcomes, adverse events, and human subjects risk in totality.

### Proposed statistical methods

Patient characteristics will be reported using descriptive statistics and frequency distributions. Continuous variables will be compared using independent samples *t*-test or Mann–Whitney *U* test, and categorical variables will be compared using chi-square test or Fisher’s exact test.

AWP will be calculated as proportion (with 95% confidence intervals [CI]) of patients with possible or definite events, as done before [19, 20, 57]. Adjudicator agreement will be assessed, per prior approach, with two-way, random effects, intraclass correlation coefficient for absolute agreement according to 0 = no awareness, 1 = possible awareness, and 2 = definite awareness. All analyses will be intention to treat, such that all patients will be evaluated, regardless of clinician adherence during the intervention phase. The unit of randomization will be the ED, and the unit of analysis will be the patient. The primary analysis will compare the proportion of patients with AWP in the control phase versus the intervention phase. To estimate the intervention effect, mixed effects models and generalized estimating equations (GEE) are most commonly used in stepped wedge designs. However, due to the smaller number of clusters (*n* = 5), it is more appropriate to use a generalized linear model, with cluster included as a fixed effect (i.e., a logistic regression model for binary outcome data with each of five sites as fixed effect) [75–78]. We will first fit a basic model, in which the intervention effect is estimated, adjusting for secular trends (i.e., time effect). We will then extend the basic model by incorporating and testing appropriate interaction terms to test the nature of the intervention effect. Examples include (1) an intervention-by-cluster interaction for heterogeneity of the intervention effect across clusters; and (2) an intervention-by-time for heterogeneity of the intervention effect across time. A possible delayed intervention effect will be tested by changing the intervention indicator (i.e., 0 or 1) into some fractions between 0 and 1, aligned with the time from switching from control to intervention. Unadjusted analyses will also be reported.

Instrumental variable (IV) methods will be used to account for non-adherence, as there could be differences between intervention effectiveness (i.e., effect among all patients to whom the intervention is targeted) and efficacy (i.e., effects among patients whose clinicians adhere to the intervention). We will use a non-parametric IV estimator adapted to stepped wedge designs, and IV regression methods to estimate complier average causal effect (CACE) of the intervention [79]. To avoid conflating the effect of time with the intervention effect, we will (1) obtain step-specific CACE estimates and (2) summarize step-specific estimates across all steps. We will also use two-stage residual inclusion to perform IV regression, using individual data from all six time points, adjusting for time and cluster effects [80–82]. Unlike per-protocol analyses, CACE analyses are not biased by selection effects and have been shown to be valid inferential approaches in stepped wedge trials [79].

We will determine proportion (with 95% CIs) of patients with clinically significant PTSD symptoms (PCL-5 score > 32) at 30 days and 180 days post-discharge [83, 84] and compare the control versus the intervention phase. To test the independent association of AWP (main exposure of interest) with 30-day PTSD symptom development, multivariable logistic regression will be used, with covariates selected for inclusion a priori [85]. The model will be adjusted for covariates previously associated with PTSD symptoms in critical illness survivors: (1) age; (2) sex; (3) prior psychological trauma (PC-PTSD-5 score)/mental health history; (4) illness severity; and (5) receipt and dose of benzodiazepines [10, 25, 26, 62, 86, 87]. We will adjust for race, given known racial disparities in PTSD symptoms [88–91]. To examine time trends in PTSD symptoms, and independent effects of AWP on time trends, mixed effect logistic regression will be used. Individual random intercept and random time slope will be specified and tested along with other potential risk factors. We will identify individual-level potential risk factors which could explain variation in individual time trend by testing interaction between random time slope and risk factor(s). In all of these models, cluster effect will be modeled as a fixed effect, using cluster indicator in the model. Similar analyses will be conducted for the other secondary outcomes.

Using structural equation modeling, we will test if patient-perceived threat mediates the relationship (i.e., on the causal pathway) between patient perception of clinician compassion and PTSD symptoms (PCL-5 as a continuous variable) at 30 days. To test for mediation, we will calculate the direct effect of patient perception of compassion on PTSD symptoms, as well as the indirect effect of patient perception of compassion on PTSD symptoms that passes through patient-perceived threat, using bootstrapped standard errors and 95% confidence intervals (Fig. 4) [92, 93]. We will perform separate analyses to also test associations between family/friend emotional support [adjusting for support persons physically present (yes/no)] with perceived threat and PTSD symptoms.

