**Fig. 1 Fig1:**
[figure not shown]
Important risk factors for awareness with paralysis include sedation under dosing, neuromuscular blocker use, and a lack of protocolled monitoring of sedation depth. Every major risk factor for awareness with paralysis commonly occurs in the emergency department

The data cited above provided our research group with the preliminary data to justify further study of AWP among mechanically ventilated ED patients. The ED-AWARENESS Study was a single-center, prospective cohort study which consecutively enrolled 383 mechanically ventilated ED patients over a 12-month period at a large academic medical center [19, 20]. Among survivors given NMB in the ED, the proportion of patients experiencing AWP was 3.3% (10/306; 95% CI, 1.6–5.9%) [19]. In an a priori secondary analysis of the multicenter ED-SED Pilot Trial, we demonstrated that 4.1% (13/314; 95% CI, 2.2–7.0%) of survivors that were given a NMB in the ED experienced AWP [21–23]. Finally, in a single-center prospective cohort conducted at Hennepin County Medical Center (an enrolling site for the current trial), the proportion of patients experiencing an AWP event was 7.4% (66/886; 95% CI, 5.8–9.4%) [24]. Taken as a whole, these data justify a clinical trial aimed at prevention of AWP among mechanically ventilated ED patients and strongly suggest the ED could be a high-yield arena in which to improve patient-centered clinical outcomes.

Psychological trauma and PTSD are a significant burden among the critically ill. PTSD is the development of significant distress or social impairment in someone directly or indirectly exposed to death, threated death, injury, or violence. Critical illness is psychologically traumatic, and 25–35% of survivors experience PTSD [25–27]. These survivors have worse quality of life, greater frequency of pain and substance abuse, increased healthcare cost, and threefold greater risk of death [28–33].

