**Fig. 2 Fig2:**

Example novel paradigm and hypothesized causal pathway for improving patient-centered outcomes. It is possible that by addressing the early period of critical illness in the emergency department, modifiable targets (increasing provider compassion, decreased patient-perceived threat, preventing awareness with paralysis) can be used to improve patient-centered clinical outcomes

There is significant rationale to target rocuronium use in the ED as a means to prevent AWP. In the ED-AWARENESS Study and ED-SED Pilot Trial, 19/23 (92.6%) AWP patients received rocuronium [19, 23]. In multivariable analysis, rocuronium was independently associated with AWP (adjusted odds ratio, 6.05; 95% CI, 1.46–17.56) [19, 23]. Importantly, AWP was not associated with other sedation-related variables, including (1) sedation monitoring; (2) analgesics, sedatives; or (3) sedation depth. This confirms that a proposal to target ED-based rocuronium may have the greatest chance to improve safety and prevent AWP. This is critical as data from the National Emergency Airway Registry (*n* = 17,583) show rocuronium use was 5% for intubations in 2002, yet up to ~ 45% by 2012 [14]. Use was up to 49% in our ED SED Study, and 60% in the ED-SED Pilot Trial [17, 21]. This indicates that AWP is likely a growing health problem. Contrary to a 5-min duration of succinylcholine (the historical default NMB), rocuronium can paralyze for up to 150 min, greatly increasing AWP risk. In addition, in clinical trials comparing rocuronium versus succinylcholine, with respect to intubating conditions, data has either favored succinylcholine or shown no difference in outcomes [43–45]. However, other preliminary work from our research team did not show an association between rocuronium and AWP risk, but rather pre-intubation mental status [24]. This suggests equipoise in the data and further confirms the need for this large-scale clinical trial.

Our objective is to conduct a pragmatic clinical trial aimed at limiting rocuronium exposure in order to reduce the proportion of mechanically ventilated ED patients experiencing AWP. We hypothesize that limiting rocuronium exposure in the ED, using succinylcholine as the default NMB of choice, will significantly reduce the proportion of patients experiencing AWP.

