### Data

Patient-level data will be easily accessible from the electronic medical record. The following baseline characteristics will be collected: age, gender, race, weight, height, pre-existing comorbid conditions, vital signs at presentation, and pertinent laboratory variables. Pre-intubation mental status, drugs used to facilitate intubation, and ventilator settings in the ED will be collected. After the initiation of mechanical ventilation in the ED, all medications related to analgesia and sedation in the ED will be collected. Sedation depth in the ED will be recorded by bedside nurses, using validated sedation depth scales, such as RASS or the sedation-agitation scale (SAS), per existing protocols [70].

The following in-hospital data will be collected: duration of ventilation, agents used for analgesia and sedation during the first 24 h of ICU admission, depth of sedation during the first 7 days after admission, lengths of stay in the ICU and hospital, discharge location, and mortality status (Table 1).

**Table 1 Tab1:** Schedule of screening, data collection, and outcomes assessments for the ED-AWARENESS-2 Trial

Measurement/event	ED	Extubation	^a^1	2	3	4	5	6	7	MV^b^	HOSP D/C	Day 30	Day 180
Inclusion criteria	X												
Exclusion criteria		X											
Demographics, baseline data	X												
Laboratory values	X												
Blood gas values	X		X										
ED procedures and care	X												
Intubation meds and location	X												
Safety events (i.e., intubation success, unplanned extubation, cardiac arrhythmia, allergy, MH)	X												
Ventilator settings/data	X												
Sedation depth (RASS, SAS), documented by bedside nurse	X		X	X	X	X	X	X	X				
Medications for sedation, analgesia, NMB	X		X										
Delirium assessment/CAM-ICU			X	X	X	X	X	X	X				
Assessment of AWP		X											
Ventilator duration										X	X		
Length of stay (hospital and ICU)											X		
Discharge location											X		
Mortality status											X		
Mental health and QOL assessments												X	X

*ED* emergency department; *MV* mechanical ventilation; *MH* malignant hyperthermia; *RASS* Richmond Agitation-Sedation Scale; *SAS* Sedation-Agitation Scale; *NMB* neuromuscular blockade; *CAM* confusion assessment method; *ICU* intensive care unit; *QOL* quality of life

^a^The numbers 1–7 refer to hospital days, with hospital day 1 referring to the first day after admission from the ED

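### The stated AWP model adjusts only for site and time; pre-specifying the already collected pre-intubation mental status would be a cheap safeguard against a case-mix shift at crossover

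*Protocol article*

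**What the plan says.** Proposed statistical methods describes the primary AWP model as "a logistic regression model for binary outcome data with each of five sites as fixed effect", with the intervention indicator and an adjustment for time: "We will first fit a basic model, in which the intervention effect is estimated, adjusting for secular trends (i.e., time effect". The next step is limited in kind: "We will then extend the basic model by incorporating and testing appropriate interaction terms to test the nature of the intervention effect". The examples given are intervention-by-cluster and intervention-by-time interactions, followed by a delayed-effect coding. Unadjusted results are also to be reported. No patient characteristic is named for this model.

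The Background reports three prior cohorts. The largest comes from one of the five trial sites and had 66 events in 886 patients (7.4%). The other two had 10/306 and 13/314. Later in the Background, work by the same team with the same citation as that largest cohort is said to have found something different from the other two: it "did not show an association between rocuronium and AWP risk, but rather pre-intubation mental status". The protocol presents this as evidence of equipoise.

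The Data section states: "Pre-intubation mental status, drugs used to facilitate intubation, and ventilator settings in the ED will be collected". For the secondary question of whether AWP predicts PTSD symptoms, the protocol does name patient covariates: "multivariable logistic regression will be used, with covariates selected for inclusion a priori".

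**The concern.** The protocol itself offers mental status before intubation as the rival explanation for AWP. The cohort behind it has 66 events, against 10 + 13 = 23 in the other two together, and comes from a trial site. The variable is measured before intubation and will be in the database, but the stated model does not use it.

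The model protects against two kinds of case-mix difference: those fixed within a site, and those that move over time in all sites alike. It does not protect against a change within a site that starts when the site crosses over. The design leaves two routes for such a change:

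- **Chance.** There are five clusters, and one crosses at each step, so randomization of the order can do little to balance case mix by site and period.
- **Eligibility settled after crossover.** Inclusion requires an NMB in the ED. Exclusion covers death before extubation and neurologic deficits that prevent assessment, and Table 1 places it at extubation. Clinicians do not know of the study in the control phase, but after crossover they are educated, alerted and sent monthly reports.

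At stake is how credible a result resting on few events would be if the two phases turned out to differ in how alert patients were.

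**Working it through.** **The plan's own figure.** The concern disputes no number, but the sample size fixes the layout. The inputs from Sample size justification are 3.3% versus 0.6%, ICC 0.001, 5 sites, 6 periods, 80% power and α 0.05 (two-sided assumed). I used the Hussey–Hughes variance with residual variance 0.033 × 0.967 = 0.03191 and 103 patients per site-period:

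- σ² = 0.03191/103 = 0.0003098; τ² = (0.001/0.999) × 0.03191 = 0.0000319
- Design sums: U = 15, W = 55, V = 55
- Variance = 5σ²(σ² + 6τ²) / [(5U − W)σ² + (U² + 30U − 6W − 5V)τ²] = 5σ²(σ² + 6τ²) / (20σ² + 70τ²) = 0.0000921, so SE = 0.00960
- Power = Φ(0.027/0.00960 − 1.96) = Φ(0.853) = 80.3%

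So 30 × 103 = 3090 is reproduced.

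**Events and parameters.** Each phase has 15 cells × 103 = 1545 patients. Expected events are 1545 × 0.033 + 1545 × 0.006 = 51.0 + 9.3 = 60.3. With categorical periods the model has 1 + 4 + 5 + 1 = 11 parameters, or 5.5 events per parameter. One added covariate gives 60.3/12 = 5.0.

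**Size of a crossover-aligned shift.** These inputs are assumptions, because the protocol gives no prevalence, strength or direction: half of patients alert, higher AWP risk in alert patients with odds ratio R = 3 to 5, overall risk 3.3%, and no true intervention effect.

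- Solve (p₀ + p₁)/2 = 0.033 with odds(p₁) = R × odds(p₀). R = 3 gives p₀ = 0.0169 and p₁ = 0.0491. R = 5 gives 0.0114 and 0.0546.
- If the alert share is q in intervention cells and 0.5 in control cells, the intervention risk is r = (1 − q)p₀ + q·p₁. The spurious odds ratio is [r/(1 − r)] / (0.033/0.967).

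| Shift in all sites | R | r | Spurious OR | SE of log OR | Null rejection |
|---|---|---|---|---|---|
| +10 points | 3 | 0.0362 | 1.10 | 0.353 | 5.9% |
| +10 points | 5 | 0.0373 | 1.14 | 0.351 | 6.5% |
| −10 points | 3 | 0.0298 | 0.90 | 0.370 | 5.9% |
| −10 points | 5 | 0.0287 | 0.87 | 0.374 | 6.7% |
| −20 points | 3 | 0.0266 | 0.80 | 0.381 | 9% |
| −20 points | 5 | 0.0244 | 0.73 | 0.389 | 13% |

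The SEs and rejection rates come from fitting the site + period + intervention logistic model to expected counts in 30 cells of 103. With the covariate added, every row returns an odds ratio of 1.00 and 5% rejection, because mental status is the only thing that shifts.

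**Other assumptions.** With 40% alert and R from 2 to 6, a 10-point drop gives 0.93 to 0.83, and a 20-point drop gives 0.86 to 0.67 (rejection 6.9% to 17.5%). If only one site shifts by 20 points (50% alert, R = 3 to 5), the odds ratio is 0.97 to 0.93 and rejection is at most 5.5%.

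**What the stated model already handles.** A 20-point drift over calendar time in all sites, or fixed site differences of up to 20 points either way from the average, gives a null odds ratio of 1.00 without the covariate.

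**No shift, design effect present.** The design log OR is ln(0.006/0.994) − ln(0.033/0.967) = −1.73 (OR 0.18). With 50% alert and R = 3 to 5, the SE is 0.559 to 0.560 without the covariate and 0.561 with it. Power is about 87% either way.

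**The case against.** The strongest reply is that nothing here is wrong. A randomized comparison does not need a prognostic covariate to be valid, and this is a condensed article whose analysis plan is not shown and may list adjusted or sensitivity models. The PTSD model names covariates because it is an observational association, so the contrast proves little. The Background also reports an adjusted odds ratio of 6.05 for rocuronium from the other two cohorts; the mental-status finding comes from one centre. All eligible consecutive patients are to be enrolled, the order of crossover is randomized, and nothing in the protocol says alertness changes at crossover. All of this stands. It makes the point an improvement and not a defect.

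A reader might go further and infer any of the following, none of which the documents support:

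- **That the primary result is biased.** This needs a shift aligned with crossover, and none is documented.
- **That power suffers materially.** At the plan's rates it is about 87% with or without the covariate, and the protocol specifies no smaller intervention effect.
- **That type I error is out of control through random case-mix variation.** In simulation (4,000 null runs per scenario), an extra site-period SD of 5 points gave the same error with and without the covariate (5.1% at R = 3, 5.7% at R = 5). A clear gap (6.8–7.9% versus 5.4–5.8%) appeared only at an SD of 20 points. That is about four times the sampling SD of √(0.25/103) = 4.9 points.
- **That adjustment would cure selection through post-crossover eligibility.** It removes only the part that runs through mental status.

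What the reply does not remove is that the protocol names this predictor, collects it, and fixes a primary model without it. A covariate chosen after the data are seen would carry less weight.

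**Conclusion.** The point holds as a low-cost improvement in robustness, not as an error in the plan. The gap in the stated model is narrow: a change in mental-status mix that coincides with crossover.

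Under the main assumptions, a 10-point rise biases the log odds ratio by +0.10 to +0.13. That is about 6% to 7% of the design effect of 1.73 in absolute size. Even the most extreme case tried (OR 0.67) is far from 0.18. Such a bias would matter more if the true effect were smaller than planned. If alert patients had the lower risk, the directions would reverse. All sizes rest on an assumed prevalence and odds ratio, and those in the table also on a shift in every site.

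**What to change.** Add pre-intubation mental status as a fixed covariate to the site + period + intervention model for AWP. Define one coding in advance, for example normal versus impaired, with a category for missing values. Report the model without the covariate alongside it. If the basic model is to stay primary, the adjusted model should at least be named before the data are examined.

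The cost is one or two parameters. With about 60 expected events, events per parameter fall from 5.5 to 5.0 with one added parameter, or to 60.3/13 = 4.6 with two. In the check with one parameter, precision and power were essentially unchanged. No new data collection is needed.
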